### Rationale for LVSD case definition

1.3.

Definitions of cardiotoxicity vary according to clinical trials and guidelines. The most commonly accepted definition of clinically significant cardiotoxicity in adults is a >10% decrease in LVEF to an LVEF < 50% (50). Baseline cardiac dysfunction or cardiovascular comorbidities are uncommon in pediatrics, thus pediatric definitions commonly rely on an absolute LVEF or LVFS without taking into account the decline from baseline. The Common Terminology Criteria for Adverse Events (CTCAE) definitions of LVSD have varied over time but have generally defined grade 2 or higher LV dysfunction using an LVEF threshold of 50% (termed “ejection fraction decreased” in CTCAE v. 5). Therefore, LVSD cases will be defined by an LVEF < 50% for all AAML1831 cardiac analyses. The first cardiac aim (described below) includes all subjects treated on Arms A/B using site-measured/reported LVEF to determine LVSD (*n* = ∼1,068). The second cardiac aim is limited to a subcohort of representative subjects who will undergo detailed cardiac phenotyping via core lab echocardiography quantitation and serial cardiac biomarker assessment (*n* = ∼510).

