### Subjects

3.1.

Eligible patients included those aged less than 22 years at the time of study enrollment with newly diagnosed AML according to the 2016 WHO classification (51). The subjects must also have one of the following: >20% bone marrow blasts, <20% bone marrow blasts with one or more defining genetic abnormalities listed by the study, or at least 1,000/µl circulating leukemic cells. The subjects with cardiac dysfunction, defined as LVEF <50% or LV shortening fraction less than 24%, are not eligible to participate. Additional exclusion criteria include germline AML predisposition syndrome, concurrent malignancy, or any of the following myeloid leukemias: juvenile myelomonocytic leukemia, Philadelphia chromosome-positive AML, mixed-phenotype acute leukemia, acute promyelocytic leukemia, AML arising from myelodysplasia, or therapy-related myeloid neoplasms. Receipt of prior anti-cancer therapy is prohibited unless specified in the protocol. All patients and/or their parents or legal guardians must provide written informed consent.

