#### Echocardiograms

3.3.1.

Cardiac function will be serially assessed by echocardiograms at baseline, following each subsequent therapy cycle, 12 months following completion of protocol therapy, and at least every 2 years thereafter through 10 years following completion of protocol therapy (Figure 2). Additional echocardiograms are required for patients with FLT3-mutant AML receiving gilteritinib maintenance, including pre-, mid- (week 25), and postmaintenance. Pre-/postcycle echocardiograms are to be performed when the patient has recovered from the toxicities of the previous chemotherapy cycle and ideally when off IV fluids and with evidence of blood count recovery. Echocardiograms are to be performed according to the AAML1831 echocardiogram acquisition protocol, reflective of a contemporary and comprehensive standard-of-care pediatric echocardiogram. Emphasized views include the 2D LV images in the apical four-chamber, two-chamber, and three-chamber views and the parasternal short-axis views at the LV apex, mid-, and basal levels. Site sonographers are recommended to review the AAML1831 echocardiogram acquisition training slides or webinar and undergo a certification process involving detailed feedback from the core lab regarding echocardiogram quality. Echocardiograms are analyzed for LV function at each site per standard-of-care to inform clinical care and safety of ongoing anthracycline delivery. Each site-measured LVEF and LVSF are required to be submitted in the AAML1831 case report forms. DICOM echocardiogram images are submitted to the Penn Center for Quantitative Echocardiography for post hoc quantitation in a blinded fashion. The primary measurements include LVEF derived by biplane Simpson's method, global longitudinal and circumferential strain, and LV wall thickness (LVWT) to LV end-diastolic dimension (LVEDD) ratio. Additional comprehensive measures of cardiac structure and function relating to chamber size, Doppler indices, and valvular disease are also obtained, which will enable important exploratory analyses of the impact of AML therapies on cardiac remodeling, systolic and diastolic function, as well as more novel indices such as regional strain (53, 54). All measures are quantitated using the Tomtec cardiac performance analysis (Unterschleissheim, Germany).

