#### Cardiotoxicity risk prediction

3.5.2.

For analysis of cardiotoxicity predictors, a case cohort will be constructed composed of a subcohort of sequentially enrolled patients treated on arms A and B (*n* = 510 including 84 high-risk and 171 low-risk patients per arm), plus any additional LVSD cases identified from the Arm A/B study population outside of the subcohort based on site measured LVEF and confirmed on core lab quantitation. LVSD cases will be defined as a centrally measured core lab LVEF < 50% or, if LVEF is not available, LVFS < 24% at any precycle, end-of-therapy, or off-therapy echocardiogram between intensification and 12 months posttherapy.

Among the case cohort (*n* = 543), a series of weighted ordinary least-squares linear regression models will be used to define the association between postinduction 1 GLS and the postinduction 1 change from baseline in GLS (two separate models) and LVEF at 12 months posttherapy (dependent variable). A similar series of regression models will be used to assess the association between on-therapy hs-cTnT and NT-proBNP elevations (predictors) with EF 12 months after therapy (outcome variable).

Subsequently, time-to-event survival models will be used to estimate the relationships of relevant host factors (age, sex, BMI, race) and treatment exposures (cumulative anthracycline dose, anthracycline arm, HSCT vs. chemotherapy alone) with LVSD, defined as core lab quantitated LVEF < 50% occurring on or within 1 year after protocol therapy. After the estimation of the relationship of these host and treatment variables with LVSD, a multi-marker risk prediction model will be developed incorporating significant host factors, treatment exposures, and echocardiographic predictors for the development of LVSD within 1 year of completing therapy. Finally, a separate cohort of children treated on AAML1031 will be retrospectively analyzed to provide external validation for this risk prediction model.

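### The core-lab LVSD case rule in section 3.5.2 has no core-lab baseline condition, so some subcohort patients already below 50% before treatment can count as newly developed LVSD

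*Protocol article*

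**What the plan says.** **Entry (section 3.1, Subjects).** "The subjects with cardiac dysfunction, defined as LVEF <50% or LV shortening fraction less than 24%, are not eligible to participate". The section does not name the reader.

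**Who reads, and when (section 3.3.1, Echocardiograms).** Sites read for care: "Echocardiograms are analyzed for LV function at each site per standard-of-care to inform clinical care and safety of ongoing anthracycline delivery". The core lab reads later: "DICOM echocardiogram images are submitted to the Penn Center for Quantitative Echocardiography for post hoc quantitation in a blinded fashion".

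**Case rule for risk prediction (section 3.5.2).** "LVSD cases will be defined as a centrally measured core lab LVEF < 50% or, if LVEF is not available, LVFS < 24"%, on any precycle, end-of-therapy or "off-therapy echocardiogram between intensification and 12 months posttherapy". Cases added from outside the subcohort must be "based on site measured LVEF and confirmed on core lab quantitation".

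**Outcome of the time-to-event models (section 3.5.2).** LVSD is "defined as core lab quantitated LVEF < 50% occurring on or within 1 year after protocol therapy".

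**Reason for an absolute threshold (section 1.3).** Baseline dysfunction is described as uncommon in children, so "pediatric definitions commonly rely on an absolute LVEF or LVFS without taking into account the decline from baseline". The article adopts LVEF below 50% for all its cardiac analyses.

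**The concern.** An absolute threshold identifies new disease only if everyone starts above it on the same measurement scale. Here the entry screen and the outcome use different readings of LVEF. The section 1.3 rationale explains why no decline criterion is used, but it does not deal with this change of reader. The article itself treats the two readings as different in quality: its Discussion credits core-lab interpretation with less variability.

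The aims are worded in terms of incident disease: predictors of subsequent LVSD (section 2) and the development of LVSD within a year of completing therapy (section 3.5.2). A child read as 53% by the site and 48% by the core lab at baseline is eligible. If that child is in the subcohort and the core lab reads 48% again in the window, the rule records a case although nothing changed. Such a child would tend to have low early strain values as well. Echocardiographic predictors could then look better at forecasting treatment injury than they are. With few cases expected, a handful of such patients can matter.

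**Working it through.** **1. The plan's own counts.** The subcohort has 2 × (84 + 171) = 510 patients, 255 per arm. Expected subcohort cases are 255 × 0.08 + 255 × 0.05 = 20.4 + 12.75 = 33.15 (stated 33). The case cohort is 510 + 33 = 543 (stated 543). The stated 66 cases in total follow from 1,020 patients: 510 × 0.08 + 510 × 0.05 = 66.3. (The approximate 1,068 of section 1.3 would give 69.4; this does not affect the present point.)

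**2. What the rule requires.**

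| Step | Reading used | Core-lab baseline condition |
|---|---|---|
| Entry | Site (core lab is post hoc) | none possible |
| Subcohort case | Core lab, intensification to 12 months off therapy | none stated |
| Case from outside the subcohort | Site, then core-lab confirmation | none stated |
| Time-to-event outcome | Core lab, on therapy or within 1 year after | none stated |

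The baseline echocardiogram lies outside the case window, so a low baseline is not enough. The patient must read below 50% again later.

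**3. Illustrative size.** The documents give neither a core-lab baseline mean nor site/core-lab agreement, so every input here is an assumption. Model: true LVEF T ~ N(μ, 5²); each reading = T + independent error with SD e; keep patients with site baseline ≥50; no treatment effect; k later core-lab echocardiograms. Low baseline means P(core baseline <50 | site baseline ≥50) × 510. A case on top of a low baseline also needs at least one of the k later core-lab readings to be below 50. Simulation (1 million patients per setting), per 510:

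| μ | e | Low core-lab baseline | ...and a case, k = 3 / 5 | Normal baseline, case by reading error alone, k = 3 / 5 |
|---|---|---|---|---|
| 64 | 4 | 5.8 (1.1%) | 2.1 / 2.7 | 12.9 / 19.3 |
| 64 | 5 | 10.1 (2.0%) | 3.4 / 4.6 | 23.2 / 34.8 |
| 62 | 4 | 11.5 (2.3%) | 4.8 / 6.2 | 23.8 / 35.3 |
| 62 | 5 | 18.5 (3.6%) | 7.5 / 9.7 | 38.8 / 57.1 |

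About 6–18 patients have a low core-lab baseline, but only about 2–10 become cases. Against the plan's expected number, that is 2.1/33.15 = 6% to 9.7/33.15 = 29%.

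**4. Sensitivity to the assumptions.** With means of 60–65%, core-lab SD 5.7–10 and site/core-lab correlation 0.44–0.64, the count of such cases runs from 0.4 to 36 per 510.

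**5. Cases from outside the subcohort.** If site and core lab must both read below 50% on the same later echocardiogram, the 2–10 falls to about 1–4 per 510.

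**6. What a baseline condition would remove.** Under the same noise it removes 4.6/(4.6 + 34.8) = 12% to 4.8/(4.8 + 23.8) = 17% of all cases that arise without any true change.

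**The case against.** The strongest reply is that this is a condensed article, that defining the at-risk set belongs to the full protocol or SAP, and that time-to-event language already implies patients free of the event at time zero. That has some force. But section 3.5.2 fixes the reader, threshold, fallback and window, and the rule as written admits these patients. The absolute threshold is a declared choice and is not itself at fault.

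Other parts of the reply stand and set the limits of the point:

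- A reader might infer that the comparison between arms is biased. The documents do not support that. Aim 1 uses site LVEF, the same scale as entry, and aim 2 compares serial core-lab measurements by GEE.
- A reader might infer that the specified GLS regressions are inflated. Their dependent variable is continuous LVEF at 12 months, so the LVSD definition reaches them only through which cases are sampled.
- A reader might set the 6–18 low baselines against the 33 expected cases. Those are low baselines, not false cases.
- A reader might apply the concern to all 66 expected cases. The 33 from outside the subcohort must also be cases on the site reading, so they are largely protected.

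The size model is also open to attack. Both readers see the same baseline images, so their errors need not be independent. The shortening-fraction exclusion is ignored. The core lab is given the sites' error. At the noisier settings, reading error alone produces more cases than the 33 expected.

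**Conclusion.** The point holds for the core-lab LVSD case definition and for the LVSD time-to-event and risk-prediction models. As written, subcohort patients who are below 50% on the core-lab scale before treatment, and below it again in the window, count as newly developed LVSD. That entry rests on the site reading is an inference from the post hoc timing of core-lab work, but no other reading is available then. The size cannot be fixed from the documents. About 2–10 of 510 against 33 expected is a plausible illustration under a baseline mean of 62–64%, true SD 5 and error SD 4–5. Wider assumptions run from negligible to large. The correction is worth making because the rule does not match the stated target of incident LVSD and the remedy is cheap. The trial's randomised cardiac comparisons are not in question.

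**What to change.** In the core-lab LVSD time-to-event and prediction models, define the at-risk set as patients with core-lab baseline LVEF of at least 50% or, where LVEF is unavailable, LVFS of at least 24%. Apply this alike to subcohort members and to cases added from outside. Report the number excluded by arm, and give the analysis without the exclusion as a sensitivity analysis. Where core-lab baselines exist in the AAML1031 validation cohort, apply the same condition there.

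Cost: this changes an analysis definition only. Baseline echocardiograms are scheduled for everyone, and the model of GLS change from baseline already needs the core-lab baseline reading. The case count will fall slightly, and some site-eligible children leave the model on the strength of one noisy reading, which is why the unrestricted analysis should be kept. The article does not say whether AAML1031 core-lab baselines are available. The change does not remove cases created by reading error after a normal baseline, which were the larger group in the illustration.

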#### Secondary cardiac measures

1.2.2.

The application of newer metrics, such as blood biomarkers and novel echo indices, is an area of active investigation to identify vulnerable patients prior to overt and/or irreversible cardiac remodeling and dysfunction (35, 36). Therefore, AAML1831 will utilize sensitive echocardiographic measures and cardiac biomarkers to (a) compare the impact of cardiotoxic therapies across arms and (b) complement patient- and treatment-specific variables to identify individuals at high cardiovascular risk.

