i.*Strain echocardiography* is a sensitive measure of cardiac deformation that offers direct insight into myocardial mechanics and contractility (37). Studies performed in a variety of heart failure populations suggest that global longitudinal strain (GLS) is the first dimension of myocardial deformation to become impaired, potentially reflecting the vulnerability of the subendocardium (38). Numerous adult oncology studies have shown that early GLS declines predict subsequent LVEF declines (39–41). GLS declines have also been observed in childhood cancer in both the acute and long-term follow-up setting after anthracycline therapy (26, 42–44). Collectively, these findings indicate a likely role for strain as a meaningful early measure of cardiotoxicity during childhood AML therapy and support its inclusion as a sensitive assessment of cardiac function (outcome variable, cardiac aim 2) and an early predictor of more advanced declines in LVEF (predictor variable, cardiac aim 3).ii.*Cardiac biomarkers:* Pediatric studies have demonstrated the prevalence of troponin and natriuretic peptide elevation during anthracycline therapy and their association with subsequent adverse cardiac remodeling (45). In addition, early troponin elevations in adult cancer patients predict subsequent cardiac events (46). Although these studies suggest the utility of troponin for early detection of anthracycline-induced cardiac injury, the specific patterns of biomarker elevations that predict progression to heart failure have not yet been determined in children. Therefore, serial biomarker analysis may help clarify the role of these blood biomarkers in predicting cardiotoxicity. Although there may be differences in troponin T as compared to troponin I in the cancer population, troponin T has been extensively studied in the pediatric population, and both markers are associated with prognosis in the cardiovascular population (45, 47–49). Moreover, blood will also be banked for future assays.

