## Cardiac aims

2.

The AAML1831 cardiac studies were designed to address the high rate of cardiotoxicity in children who have undergone treatment for AML. The methods and planned analyses were specifically designed to address several secondary and exploratory study aims included in AAML1831.

First, to compare the cardioprotective efficacy of dexrazoxane vs. liposomal anthracycline encapsulation, the AAML1831 cardiac studies will compare the incidence of LVSD in children with non-FLT3 mutant *de novo* AML treated with standard daunorubicin and dexrazoxane-containing induction (Arm A) vs. CPX-351-containing induction (Arm B) (cardiac aim 1). Changes in serial centrally quantitated, echocardiography-derived measures of cardiac function (including LVEF and GLS) and biomarkers of cardiomyocyte stress and injury (including natriuretic peptides and troponin) will be similarly compared across arms A vs. B (cardiac aim 2). To identify predictors of cardiotoxicity, AAML1831 analyses will determine if early changes in sensitive echocardiographic measures of cardiac function (e.g., GLS and elevation of circulating cardiac biomarkers) are associated with subsequent declines in LVEF (cardiac aim 3). An exploratory aim of cardiac studies is to quantify associations between host factors (age, sex, BMI, race), treatment exposures (cumulative anthracycline dose, anthracycline arm, HSCT vs. chemotherapy alone), early declines in GLS, and elevations in cardiac biomarkers (high sensitivity troponin T (hs-cTnT) and N-terminal pro-B-type natriuretic peptide (NT-proBNP)) with subsequent LVSD. These data will then be used to develop a multi-marker risk prediction model incorporating significant host factors, treatment exposures, and echocardiographic predictors for the development of LVSD within 1 year of completing therapy. These aims will be restricted to the population of non-FLT3 mutant subjects treated on Arms A/B, whereas those treated with concurrent tyrosine kinase inhibition on Arms C/D will be analyzed separately.

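### The Aim 3 linear models relate early GLS to 12-month LVEF with no stated term for LVEF on the same echo, so a positive result would not by itself show prediction of subsequent decline

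*Protocol article*

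**What the plan says.** Section 2 (Cardiac aims) asks whether early changes in sensitive echo measures such as GLS, and biomarker elevations, "are associated with subsequent declines in LVEF (cardiac aim 3"). Section 1.2.2 presents GLS as "an early predictor of more advanced declines in LVEF".

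Section 3.5.2 gives the analysis. In the case cohort of 543, weighted least-squares models are to "define the association between postinduction 1 GLS and the postinduction 1 change from baseline in GLS (two separate models) and LVEF at 12 months" after therapy. The outcome is a level, "LVEF at 12 months posttherapy (dependent variable"), not a change. No baseline LVEF, post-induction 1 LVEF or LVEF-only comparison model is mentioned. The biomarker models are described as similar.

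The missing measurement will exist. Section 3.3.1 says of the core-lab read: "The primary measurements include LVEF derived by biplane Simpson's method, global longitudinal and circumferential strain". The same section has sites read LV function on each echo as standard of care.

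For the exploratory LVSD work, section 2 lists host factors, treatment exposures, "early declines in GLS, and elevations in cardiac biomarkers". The multi-marker model then takes in echocardiographic predictors without naming them.

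**The concern.** Whether a marker predicts a later fall in LVEF is a question about what happens after the marker is read. A model of the 12-month LVEF level that holds no earlier LVEF does not isolate that. A patient whose LVEF dropped during induction 1 and stayed low has poor GLS after induction 1 and low LVEF at 12 months, and so contributes to a GLS association even though nothing further declined.

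GLS and LVEF are read from the same images and can be expected to move together. A positive result could thus mean either of two things: strain gave early warning, or strain restated a loss that LVEF on the same echo already showed. The models as described cannot tell these apart. The distinction matters because LVEF is already read before each cycle, so the practical worth of strain depends on what it says beyond that LVEF.

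**Working it through.** **Plan's own figure.** The case-cohort size reproduces. Section 3.6 assumes LVSD rates of 8% and 5%, and the subcohort has 84 + 171 = 255 patients per arm. Expected subcohort cases are 255 × 0.08 + 255 × 0.05 = 20.40 + 12.75 = 33.15 (stated 33). Adding the 33 stated cases from outside the subcohort gives 510 + 33 = 543. No power is stated for Aim 3.

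**Set-up.** Suppose GLS carries no information on 12-month LVEF beyond the LVEF on the same echo. All correlations below are assumptions, with GLS coded so that higher means better function:
- g, GLS with same-echo LVEF: 0.4 to 0.6
- r, post-induction 1 LVEF with 12-month LVEF: 0.3 to 0.5
- baseline with post-induction 1 LVEF: 0.5
- two-sided 5% test; case-cohort weights ignored

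**GLS-level model as described.** The induced correlation of GLS with 12-month LVEF is ρ = g × r. By Fisher's z, the chance of significance is about Φ(atanh(ρ) × √(n − 3) − 1.96). At n = 543, √540 = 23.24.

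| g | r | ρ | atanh(ρ) × 23.24 | chance of significance |
|---|---|---|---|---|
| 0.4 | 0.3 | 0.12 | 2.80 | 80% |
| 0.5 | 0.4 | 0.20 | 4.71 | 99.7% |
| 0.6 | 0.5 | 0.30 | 7.19 | 100% |

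Not everyone will have both echoes. At n = 350, √347 = 18.63; the first row becomes 0.1206 × 18.63 = 2.25, or 61%, and the last stays near 100%.

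**Baseline LVEF alone is not enough.** Given baseline LVEF, the partial correlation is 0.75gr / √[(1 − 0.25g²)(1 − 0.25r²)]. In the lowest case this is 0.09 / √(0.96 × 0.9775) = 0.093, and the chance is 58% at n = 543. In the highest case it is 0.244, near 100%.

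**Change-in-GLS model.** If baseline GLS relates to baseline LVEF in the same way, the change has covariance 0.5gr with 12-month LVEF and variance 2 − g². The induced correlation is 0.06 / √1.84 = 0.044 in the lowest case and 0.15 / √1.64 = 0.117 in the highest. The chance of significance at n = 543 is about 18% to 78%. With baseline LVEF alone added, it rises to about 35% to 99%.

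**With same-echo LVEF added.** Simulation of the same set-up returns about 5% for both models, as it must when GLS adds nothing.

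**Wider assumptions.** With g and r each from 0.3 to 0.7, the GLS-level model is significant in about 56% to 100% of trials at n = 543 and 34% to 100% at n = 300.

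**The case against.** The strongest objection is that silence is not exclusion. The article names predictor and outcome but no covariates of any kind, and does not call the models univariable. A full protocol or SAP may add them. That stands as a limit: a reader might infer that the trial will never set GLS against LVEF, or that GLS will wrongly be credited, and the article supports neither. But it does spell out the predictors, the outcome, the number of models and the weighting, and this term decides what the result means.

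Second, section 1.2.2 says only that the markers should "complement patient- and treatment-specific variables to identify individuals at high cardiovascular risk"; it does not promise that strain outperforms LVEF. This is fair, and an unadjusted association is legitimate description. It still does not answer a question framed as subsequent decline.

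Third, the percentages could be read as false-positive rates. They are not. Under the assumed set-up the marginal association is real, so for the association as literally stated they are power. They show how often a significant result would arise when GLS adds nothing.

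Fourth, a reader might conclude that the LVSD risk model omits early LVEF as well. The article does not establish this: the exploratory list names only GLS among early echo measures, but the model's category of echocardiographic predictors can include LVEF.

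Fifth, patients with LVEF below 50% at entry are ineligible, and case-cohort LVSD cases are counted only from intensification. Neither removes an LVEF fall during induction 1 from the linear models.

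**Conclusion.** The point holds for the two linear GLS models as the article describes them. They do not separate prediction of later decline from an LVEF fall already present after induction 1, so a positive result would not by itself support the aim as worded. Under the stated assumptions the GLS-level model is significant in about 80% to 100% of trials at n = 543 when GLS adds nothing to same-echo LVEF, against about 5% with that LVEF included; the change-in-GLS model is affected less. The structural point needs no figures. Its size rests on correlations that the documents do not give, on ignoring the case-cohort weights, and on no LVEF term being set elsewhere. GLS may well add information; the models as described would not show whether it does. The comparison of cardiotoxicity between arms is not affected.

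**What to change.** - **Linear GLS models (both).** Add core-lab post-induction 1 LVEF, together with baseline LVEF. Take the adjusted GLS coefficient as the test of subsequent decline. Keep the unadjusted association as descriptive.
- **LVSD risk model.** State that post-induction 1 LVEF is among the echocardiographic predictors, and report what GLS adds to it, for example by a likelihood-ratio test and the change in C-index.
- **Biomarker models.** Adjust for LVEF from the most recent echo at or before the sample. Day 8 samples (induction 1, and intensification 2 in the mitoxantrone strata) have no matching scheduled echo, so a same-time LVEF cannot be required.

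The cost is wording in the analysis plan. No new data are needed, because the core lab reads LVEF and strain from the same studies. The downside is that the reported GLS association will be smaller and, because GLS and LVEF are correlated, less precise.
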